## Methods

### Study design

Continuing vs withholding ACEIs/ARBs is a multi-centric, open-label, randomised controlled two-arm trial, with a 1:1 allocation of hypertensive patients undergoing major non-cardiac surgery to either continue or stop their ACEIs/ARBs. When admitted to the hospital, patients will be randomised to either continue their ACEIs/ARBs including on the day of surgery (group A) or discontinue the drugs 24–36 h before surgery (group B). The primary endpoint will be a composite outcome of all-cause 30-day mortality, major adverse cardiovascular events (acute myocardial infarction, stroke, arrhythmias requiring intervention, hypertensive crises, acute pulmonary oedema, postoperative cardiogenic shock), acute kidney injury, postoperative respiratory failure, sepsis and unplanned ICU admissions. The Standard Protocol Items: Recommendations for Interventional Trials (SPIRIT) checklist is provided in Additional file 2, and the schedule of the participant enrolment in the study (SPIRIT figure) is shown in Fig. 1.

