### Randomisation and blinding

All study patients will receive the same standards of care and management, including treatment of any harm resulting from the trial. However, they will receive no compensation as a result of participation in the study. They will be randomised to either continue with their ACEI/ARB treatment (including on the day of surgery) (group A) or to withhold it 24–36 h before surgery (group B) (two doses of the ACEI or ARB will be omitted to account for variation in the timing of administration, i.e. morning or evening). The patient’s blood pressure will be monitored periodically and treated with calcium channel blockers if necessary. Other antihypertensives that the patient may be concurrently receiving will be continued on the day of surgery. All such orders will also be recorded. Following surgery, anti-hypertensive medications including ACEIs/ARBs will be restarted at the earliest and the date of restarting anti-hypertensive therapy will be noted.

Randomisation will be carried out using permuted block randomisation (blocks of 20). The randomisation codes and sequence will be computer-generated by a statistician at each institute. The randomisation codes and the sequence will be kept secure at each participating centre. One code from a block sequence will be allotted each time when the patient is enrolled into the study. Allocation concealment will be with opaque sealed envelopes which will be opened 2 days before surgery. The diagnosis of outcomes will be made by clinicians treating the patients. The data for primary and secondary outcomes will be collected from the anaesthesia and surgical case records by the investigators and the project staff. The project staff will be trained by the investigators in the aspects of data collection and approach to missing data.

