### Clinical data

Baseline data such as age, gender, height, weight, BMI, ASA physical status, surgery, co-morbidities and anti-hypertensive medications will be collected. In-hospital mortality/mortality within 30 days of surgery, postoperative major adverse cardiovascular events (acute myocardial infarction, stroke, acute pulmonary oedema, postoperative cardiogenic shock, acute severe hypertension crisis, severe cardiac arrhythmia requiring therapeutic intervention), the incidence of intra- and postoperative (24 h) hypotension (systolic blood pressure < 90 mmHg), acute kidney injury (based on the serum creatinine item of the KDIGO criteria [9]; baseline serum creatinine will be the preoperative value), hyperkalaemia (serum potassium level > 5.5 meq/L requiring intervention), angioneurotic oedema, sepsis (suspected or culture-positive), postoperative respiratory failure and unplanned ICU admissions will be recorded.

The impact of withholding of ACEIs/ARBs on rebound pre-induction hypertension (blood pressure > 160/90 mmHg) on the day of surgery and case cancellation will also be evaluated. Intraoperatively, the episodes of hypotension will be treated with vasopressors (ephedrine, phenylephrine, norepinephrine and epinephrine). The choice of vasopressor will be left at the discretion of the anaesthesiologist. The lowest arterial pressure, duration of hypotension and total doses of vasopressors (bolus and infusion) will also be collected and reported. Other secondary outcomes noted will be myocardial injury (elevation of serum troponin-t evaluated till 12/24 h after surgery), duration of primary hospital stay and duration of ICU stay. The ancillary and post-trial care of the participants will be as per the standard of care for all patients admitted to the hospital for routine non-cardiac surgery, till their duration of stay in the hospital.

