### Efficacy end-points

The composite primary outcome and the secondary outcomes will be collected for each patient. Diagnosis of complications will be made by the treating physicians. A data adjudication committee will review the appropriateness of the collected data for each outcome measure. Members of the committee will be blinded to the group allocation and comprise non-participating clinicians from each centre.

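### Unplanned ICU admission is a primary-endpoint component, but nothing shown requires the ICU plan to be fixed before the open-label allocation is known

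*Protocol article*

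**What the plan says.** Under Study design the trial is a "multi-centric, open-label, randomised controlled two-arm trial, with a 1:1 allocation". The primary composite listed there ends with "acute kidney injury, postoperative respiratory failure, sepsis and unplanned ICU admissions", and the Objectives section gives the same components. Unplanned ICU admission therefore stands on its own: a patient with no other component event still counts.

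Clinical data gives criteria for several outcomes (creatinine-based KDIGO for kidney injury, cut-offs for hypotension and hyperkalaemia). This component is only named: "postoperative respiratory failure and unplanned ICU admissions will be recorded".

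Randomisation and blinding sets the timing and the people involved. On timing: "Allocation concealment will be with opaque sealed envelopes which will be opened 2 days before surgery". On who decides that an outcome has occurred, the same section says: "The diagnosis of outcomes will be made by clinicians treating the patients", and no blinding is stated for them. Outcome data are "collected from the anaesthesia and surgical case records by the investigators and the project staff".

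Efficacy end-points adds a safeguard: "A data adjudication committee will review the appropriateness of the collected data for each outcome measure". On masking, that section adds: "Members of the committee will be blinded to the group allocation".

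**The concern.** Most components of the composite are events in the patient. An unplanned ICU admission is partly a fact about scheduling: the same admission counts if no bed was foreseen and does not count if one was. If the plan may be made or changed in the last 2 days, people who know the allocation can, without any intent to influence the trial, decide whether a later admission is an event.

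The article gives clinicians a reason to plan with the allocation in mind. The Abstract and Background name refractory hypotension as the risk of continuing and rebound hypertension with myocardial ischaemia as the risk of stopping. A precautionary bed for a group A patient would remove events from group A and hide harm from continuing. A precautionary bed for a group B patient would act the other way and favour the trial's hypothesis.

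At stake is the comparability of the primary event count between arms. If the pre-allocation plan was never recorded, no later analysis can recover it reliably.

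**Working it through.** **Planned effect.** Inputs from Sample size calculation: 25% in the reference group, a 21% relative decrease, 80% power, 2016 patients, final alpha 0.048. I take group A (continue) as the reference, as the study hypothesis implies.

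Group B rate = 0.25 × (1 − 0.21) = 0.1975, so the planned difference is 5.25 points.

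**Reproducing the plan's figure.** Two-sided, 1:1, with mean rate p̄ = 0.22375:

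n per arm = [z₁₋α/₂ √(2p̄(1−p̄)) + z₀.₈ √(pA(1−pA) + pB(1−pB))]² / (pA − pB)²

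With z = 1.977 (alpha 0.048) and 0.842, n = 1001 per arm, or 2002 in total. This is 0.7% below 2016, so the sample size reproduces and is not in question here.

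**Baseline power.** With all 2100 patients (1050 per arm) and alpha 0.048:

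power = Φ[(d − 1.977 × SE₀)/SE₁]

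Here SE₀ uses the mean rate and SE₁ the two separate rates. For d = 0.0525, SE₀ = 0.01819 and SE₁ = 0.01815, power = Φ(0.911) = 81.9%.

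**Effect of post-allocation booking.** Let q be the share of all patients in an arm whose only primary event is an unplanned ICU admission, and r the share of these turned into planned admissions in that arm alone. The arm's composite falls by q × r. The documents give neither value. I assume q from 2% to 8% and r from 10% to 50%, with the shift in group A.

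| q | r | Shift (points) | Share of 5.25 | Group A rate | Power if design effect is true | Observed relative reduction | Two-sided type I error if no true effect |
|---|---|---|---|---|---|---|---|
| – | – | 0 | 0% | 25.0% | 81.9% | 21.0% | 0.048 |
| 3% | 10% | 0.3 | 6% | 24.7% | 77.4% | 20.0% | 0.051 |
| 5% | 20% | 1.0 | 19% | 24.0% | 64.8% | 17.7% | 0.080 |
| 5% | 30% | 1.5 | 29% | 23.5% | 54.4% | 16.0% | 0.123 |
| 5% | 50% | 2.5 | 48% | 22.5% | 33.2% | 12.2% | 0.264 |

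Worked row, 1.0 point: d = 0.24 − 0.1975 = 0.0425, SE₀ = 0.01804, SE₁ = 0.01802, power = Φ(0.379) = 64.8%.

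One assumed route to 1 point: 6% of group A would have an unplanned ICU admission, half of them have no other component, and one third of those are re-labelled: 6% × 1/2 × 1/3 = 1 point.

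The corners of the assumed grid are 0.2 points (2% × 10%; power 79.0%, type I error 0.049) and 4.0 points (8% × 50%; power 10.3%, type I error 0.580). The wide range shows how little the documents say about the size.

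**Direction.** Extra bookings in group A lower A's rate. The lost power is then power to show a benefit of withholding, and the excess type I error lies mainly on the side of continuing. Fewer bookings in group B raise B's rate and push the comparison the same way. Only relatively more booking in group B would favour withholding.

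**The case against.** The strongest reply is that the documents show an opportunity and no more. Screening and enrolment take place at the preoperative visit (Participants), so many ICU plans may exist before the envelope is opened. All patients are to receive the same standards of care. The Discussion reports similar perioperative hypotension in the two groups of the earlier cohort. Nothing links allocation to bed booking. A reader might infer that booking will differ by arm, or that the bias must work against the hypothesis; the text supports neither. This part of the reply stands.

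The article is also a condensed document. A reader might infer that the intended destination is not collected because the baseline list omits it. That list is introduced as examples, so the inference fails, and the full protocol or the case report form may define the term. What remains is that open label, envelope timing and the choice of component are all fixed in the article itself, and a definition written later helps only if the pre-allocation plan was captured.

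Third, a blinded committee reviews every outcome. It would be wrong to say that it sees only the recorded plan, because its material is not described and might include the date or reason of a booking. It can correct a wrong label. It cannot fully undo a bed genuinely booked after allocation, because that booking is a true plan in the record.

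Finally, the obvious cure, counting every ICU admission absent from the pre-allocation record, is not neutral. If precautionary beds were booked mainly for group A, patients who would never have had an unplanned admission would become group A events, and the bias would reverse towards the trial's hypothesis. This stands, and it shapes the fix.

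**Conclusion.** The point holds as a design exposure, not as a demonstrated bias. A primary event can depend on a decision that may be made by unblinded staff after allocation, and the safeguard described does not fully close that route. Size and direction are unknown. With q and r assumed, a shift of about 0.3 points is minor, and one of about 1 point is material: 19% of the planned difference and a power of about 65% in place of 82%. These figures take 1050 analysed per arm, alpha 0.048, group A as reference and a shift in one arm only. Patients with any other component event count regardless, which limits the effect. The sample size is unaffected, and the documents do not contradict themselves here. The change is a worthwhile low-cost improvement rather than the repair of an error.

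**What to change.** 1. Record the intended postoperative destination (ward, high-dependency unit or ICU) at the preoperative visit, before the envelope is opened, as a dated field on the case report form.
2. Give the adjudication committee that record with the date and reason of any ICU admission, allocation masked, and have it classify the admission as planned or unplanned.
3. Keep the committee's classification for the primary composite and prespecify two sensitivity analyses: one omitting this component, and one counting every ICU admission not on the pre-allocation record. The first cannot be moved by booking. The second captures admissions booked after allocation but can err in the opposite direction, so it should not be the primary definition. Agreement among the three would show that booking did not drive the result.

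The cost is one field and two analyses. Clinicians' bed booking is unaffected. Trial status gives recruitment as not yet begun, so the field can be in place for the first patient. It could not be reconstructed reliably afterwards.

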### Participants

We aim to enrol 2100 adult hypertensive patients undergoing elective major non-cardiac surgery under general or neuraxial anaesthesia over a period of 3 years (Fig. 2). Eligible patients will be screened and enrolled during their preoperative visit, and the project staff will follow up with the patient before surgery to ensure randomisation and compliance with the group allocation. Patients who are allocated to group A (continuing the ACEIs/ARBs) will continue to take these medications as per schedule including the day of surgery. For those who are allocated to group B (discontinuing the ACEIs/ARBs), these drugs will be omitted 24–36 h prior to surgery. Patients will then be followed up in-hospital by the investigators and at 30 days by telephonic calls by the project staff.

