### Exclusion criteria

The following are the exclusion criteria:Emergency surgery (surgical treatment needed within 48 h)Hyperkalaemia (serum potassium level > 5.5 mmol/L) during the preoperative visitPatients with severe chronic renal insufficiency as defined by estimated glomerular filtration rate < 15 mL/min/1.73 m^2^ or requiring renal replacement therapyPatients with preoperative shock (defined by the need for vasoactive drugs before surgery or a mean arterial pressure < 65 mmHg)Patients taking ACEI/ARBs for left ventricular dysfunction (ejection fraction < 50%)Uncontrolled preoperative blood pressures (systolic blood pressure > 180 mmHg and/or diastolic blood pressures of > 110 mmHg)

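### The rebound hypertension outcome is an absolute pre-induction pressure above 160/90 mmHg, but patients up to 180/110 mmHg are eligible, so unchanged high pressure is counted as rebound in both arms

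*Protocol article*

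**What the plan says.** In the protocol article, Clinical data lists among the effects of withholding to be studied, besides case cancellation, "rebound pre-induction hypertension (blood pressure > 160/90 mmHg" on the day of surgery. The cut-off is absolute. No change from an earlier pressure is required, and no condition says that the patient was at or below the cut-off before the drug was withheld.

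Under Exclusion criteria, the only upper blood pressure limit is "Uncontrolled preoperative blood pressures (systolic blood pressure > 180 mmHg and/or diastolic blood pressures of > 110 mmHg". Inclusion criteria set no lower ceiling, and Participants describes the population as hypertensive adults: "We aim to enrol 2100 adult hypertensive patients undergoing elective major non-cardiac surgery under general or neuraxial anaesthesia".

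Randomisation and blinding covers the time between allocation and surgery: "The patient’s blood pressure will be monitored periodically and treated with calcium channel blockers if necessary". It adds that such orders are recorded. Study hypothesis links rebound hypertension to case cancellation, again without a reference pressure.

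The baseline list in Clinical data does not name blood pressure, though its wording shows that the list is not exhaustive: "Baseline data such as age, gender, height, weight, BMI, ASA physical status, surgery, co-morbidities and anti-hypertensive medications will be collected".

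**The concern.** Rebound means a rise after a drug is stopped. An outcome with that name should need evidence of a rise, and this one needs only a level. The level lies inside the range in which patients may enter the trial, so some patients can meet the outcome before anything has been done to them. The same section shows that the authors set a baseline where change matters: acute kidney injury is judged against the preoperative creatinine.

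Rebound hypertension is one of the harms of withholding that the Abstract sets against the hoped-for benefit. If many counted cases are hypertension that was there all along, the reported incidence will overstate rebound in both arms, and the ratio between arms will understate the effect of withholding. A reader weighing the harms of withholding would be using a number that does not mean what its label says.

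**Working it through.** The plan states no rate or power for this outcome, so there is no figure of its own to reproduce. The check has two parts.

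**1. The thresholds side by side**

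- Eligible (Exclusion criteria): systolic up to and including 180, diastolic up to and including 110 mmHg.
- Outcome (Clinical data): above 160/90 mmHg before induction.
- Overlap: 180 − 160 = 20 mmHg systolic and 110 − 90 = 20 mmHg diastolic.

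A patient in this band at entry whose pressure does not move meets the outcome with a change of 0 mmHg, whichever arm was allocated. No other section removes such patients from the count.

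**2. Size of the dilution**

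Inputs:

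- 1008 per arm: half of the 2016 in Sample size calculation.
- Two-sided 5% level: assumed for this outcome.
- New-onset rates of 5% (continue) and 10% (withhold): assumed.
- Share q of patients above the cut-off at entry who stay above it: assumed at 10%, 15% and 20%.

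Formulas:

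- Observed rate = q + (1 − q) × new-onset rate.
- Power = Φ[(difference − 1.96 × SE₀) / SE₁], with SE₀ from the pooled rate and SE₁ from the separate rates.

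Worked case, q = 0.10:

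- Continue: 0.10 + 0.90 × 0.05 = 0.145. Withhold: 0.10 + 0.90 × 0.10 = 0.190.
- Ratio 0.190 / 0.145 = 1.31; difference 4.5 points.
- SE₀ = √(0.1675 × 0.8325 × 2 / 1008) = 0.01663.
- SE₁ = √[(0.145 × 0.855 + 0.190 × 0.810) / 1008] = 0.01660.
- Power = Φ[(0.045 − 1.96 × 0.01663) / 0.01660] = Φ(0.747) = 77.2%.
- Share of withheld-arm cases with no change: 0.10 / 0.190 = 53%.

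| q | Continue | Withhold | Risk difference (points) | Risk ratio | Power, absolute count | Power, new-onset only, 1008 × (1 − q) per arm | Withheld-arm cases with no change |
|---|---|---|---|---|---|---|---|
| 10% | 14.5% | 19.0% | 4.5 | 1.31 | 77.2% | 98.2% | 53% |
| 15% | 19.25% | 23.5% | 4.25 | 1.22 | 64.4% | 97.6% | 64% |
| 20% | 24.0% | 28.0% | 4.0 | 1.17 | 53.5% | 96.9% | 71% |

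The same formulas under milder assumptions:

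- New-onset rates of 10% and 20%, q = 20%: 28% vs 36%, ratio 1.29, power about 97%.
- The same rates, q = 30%: 37% vs 44%, ratio 1.19, power about 89%.
- Rates of 5% and 10%, with 10% above the cut-off at entry but only half of them persisting, and everyone else at the new-onset risk: 0.05 + 0.95 × 0.05 = 9.75% vs 0.05 + 0.95 × 0.10 = 14.5%, power about 90%.

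The mislabelling is present in every row. The loss of power is large only when new-onset rates are low and persistence is high.

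**The case against.** Four arguments stand against the point.

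**Randomisation.** Patients above the cut-off at entry are balanced between arms in expectation, so the difference in the proportion above 160/90 validly estimates the effect of allocation on exceeding that level. This stands. It also explains why the risk difference moves little (5 points to between 4.5 and 4.0) while the ratio moves a lot. It does not rescue the label.

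**The inputs are chosen.** The documents give neither the event rates nor the share above 160/90 at entry. This stands, and the power figures must be read as a range.

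**Rank of the outcome.** Rebound hypertension is in neither the primary composite nor the secondary objective; it is an additional evaluation. Case cancellation is listed separately, and its count does not depend on 160/90. This stands and limits the weight of the point.

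**Different purposes.** A safety ceiling for entry and an outcome cut-off need not match. That is true, but the fault is not that they differ. It is that the outcome can already be met at entry.

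A reader might go further and infer that treatment before induction ("treated with calcium channel blockers if necessary") removes rises mainly from the withheld arm and so biases the result towards no harm. The documents do not support that as a finding. Monitoring and treatment are described for all patients, no frequency by arm is given, and pressure remaining at induction despite usual care is a legitimate pragmatic outcome. The size depends wholly on what is assumed. If a quarter of continue-arm rises and half of withheld-arm rises are treated below the cut-off, 5% and 10% become 3.75% and 5.0%, ratio 1.33. If treatment is equally frequent in both arms, the ratio stays at 2.0. Such treatment would also lower some persistently high pressures and so reduce the dilution shown above.

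**Conclusion.** The point holds as a fault in the outcome definition. The two thresholds overlap by 20 mmHg in each component, no section refers the outcome to a prior pressure, and unchanged hypertension therefore counts as rebound in both arms. The consequences are a misnamed outcome, an inflated incidence and a diluted contrast. They do not include a biased difference between arms, and a claim that the trial would wrongly find no rebound goes beyond the documents.

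The dilution ranges from modest to substantial. The lower end of power, 53.5%, needs new-onset rates as low as 5% vs 10%, 20% of patients above the cut-off at entry, and all of them staying there. The primary endpoint and the sample size are unaffected. The change is worth making because it is cheap and the protocol reports that recruitment has not begun.

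**What to change.** 1. Record the preoperative-visit blood pressure on the case report form. A preoperative pressure is already needed to apply the exclusion criterion.
2. Define rebound relative to that value: at or below 160/90 mmHg at the visit and above it before induction. State whether one or both components must exceed the limit.
3. Compare pre-induction pressure between arms in all patients, adjusted for the visit value. This must accompany step 2, because a new-onset count alone misses large rises in patients who start above the cut-off; a move from 165/95 to 200/115 would not be counted.
4. Keep the absolute count above 160/90 as a separate outcome, named for what it is: hypertension at induction.
5. Report antihypertensives added between allocation and induction by arm, descriptively. They should not be scored as events, because in an open-label trial prescribing may itself depend on the allocation.

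The eligibility limit and the treatment rule stay as they are. The cost is one form field and a few sentences of definition. The one downside is that patients above the cut-off at the visit leave the new-onset count, though they remain in the adjusted comparison.
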